## Abstract

**Background:**

Homicide is the third leading cause of death for US adolescents and the leading cause among Black youth. Youth violence also contributes to significant mental health burden and educational disruption, with the highest impact in neighborhoods with limited resources. Programs that address intersecting determinants, including social factors and limited economic opportunities, may reduce violence experiences and perpetration.

**Objective:**

This protocol paper describes a community-partnered, 2-arm cluster–randomized trial across 16 neighborhoods (12 in Pittsburgh, Pennsylvania, and 4 in the Washington, DC, region) evaluating the Forging Hopeful Futures (FHF) intervention, enrolling approximately 720 youth aged 13 to 19 years.

**Methods:**

FHF comprises 12 sessions delivered over 6 to 12 weeks by trusted community facilitators and addresses conflict resolution, peer and intimate partner relationships, youth leadership, and job readiness with connections to employment and mentorship. Comparison clusters receive enhanced usual care (individual wellness check-ins). Assessments occur at baseline, the end of the program, 3 months, and 6 months post-program. Primary outcomes are violence involvement (experience and perpetration); secondary outcomes include experiences of multiple types of violence (eg, relationship abuse, sexual violence, bullying, and weapon carrying). Implementation data are collected using RE-AIM (reach, effectiveness, adoption, implementation, and maintenance)–informed tools and qualitative interviews.

**Results:**

The study was funded in October 2022, and recruitment began in July 2023. As of December 1, 2025, the study had enrolled 542 participants, with follow-up expected to continue through July 30, 2026. Data analysis for primary end points is expected on January 1, 2027. Primary analyses will estimate intervention effects on recent violence perpetration using generalized linear mixed models with random effects for neighborhood and participant, adjusting for baseline values and city. Exploratory analyses will examine mediation (eg, shifts in attitudes) and moderation (eg, baseline risk profiles).

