### Sample Size and Power

In determining the number of neighborhood clusters to include in the study, we sought to balance expected effect sizes with feasibility and budgetary constraints for a 3-year multicity study. Our selection of 16 clusters was informed by a previous cluster-RCT led by our team to evaluate the Manhood 2.0 curriculum and a pilot feasibility study of the Sisterhood 2.0 program (NCT02427061 and NCT04388696, respectively). We used these study findings to guide assumptions for our sample size calculations [34,39,40,46]. Sample sizes for each outcome were based on clinically meaningful differences between treatment groups with respect to changes in outcomes across time (ie, intervention effect). For the primary outcome of self-reported youth violence perpetration (fighting or weapon violence perpetration) in objective 1, the necessary sample size was calculated based on traditional methods that assume a fixed number of clusters. If we assume 8 neighborhoods randomized per arm with a conservative within-site correlation of 0.01, and 20% attrition at 3 months, we need 360 participants per arm (total N=720) to detect a standardized effect size of 0.39 with 80% power. This translates to a 35% relative reduction in the primary outcome, assuming a 57% rate in the control arm at 3 months. For all secondary outcomes, we have similar power to detect a standardized effect size of 0.39.

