### Statistical Analysis

Descriptive statistics will be used to summarize the sample with regard to baseline characteristics of interest. Means and SDs will be presented for continuous variables, while sample proportions will be provided for categorical variables.

Primary assessment of intervention effects will be based on intent-to-treat analyses. As-treated effect parameters will be estimated in secondary, exploratory analyses. We will conduct intervention intensity-adjusted analyses (estimating the dose that participants received) by substituting a score between 0 and 1 for the treatment group. Additionally, we will conduct per-protocol analyses, with participants exposed to “intervention as intended” in the treatment arm and all others treated as controls (ie, 0). Generalized linear mixed models will be used to account for stratification by city, correlation between youth from the same neighborhood, as well as the correlation between longitudinal observations from the same youth. SAS (Statistical Analysis System) software (SAS Institute) will be used for all statistical analyses. All hypotheses will be 2-sided tests with a significance level of 5%, and 95% CIs will accompany all sample statistics.

Participation bias will be assessed by comparing the age and race or ethnicity of youth participating in the study to each neighborhood’s overall demographics of youth (based on census tract data). Attrition analysis will be conducted by comparing youth who completed follow-up surveys with those who did not, based on demographics as well as outcomes measured at baseline. Mechanisms for missing data will be investigated by comparing important covariates between youth with and without missing data at each time point. We will characterize these mechanisms as (1) missing completely at random, (2) missing at random, or (3) not missing at random. If the nature of our missing data is ignorable (either missing completely at random or missing at random), we will use imputation methods, such as multiple imputation via chained equations, to handle dropout. Ultimately, sensitivity analyses will be conducted to compare the results of our imputation methods to complete-case and available-data analyses.

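### The stated primary model has only time-constant neighborhood and participant effects, and how baseline enters is described in two ways; on one of them the T2 test can exceed 5%

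*Protocol article*

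**What the plan says.** Protocol article, Abstract (Results): the primary analysis uses "generalized linear mixed models with random effects for neighborhood and participant, adjusting for baseline values and city". Methods, Statistical Analysis, names the same two sources of dependence, "correlation between youth from the same neighborhood, as well as the correlation between longitudinal observations from the same youth", together with stratification by city. It does not say how baseline enters.

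Methods, Measures and Table 2, defines the primary outcome as a change in violence perpetration from baseline to 3 months after the program (T2). Sample Size and Power bases the calculation on "differences between treatment groups with respect to changes in outcomes across time" and equates this with the intervention effect. The planning inputs are "8 neighborhoods randomized per arm with a conservative within-site correlation of 0.01, and 20% attrition at 3 months". Tests are two-sided at 5%.

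No section mentions a neighborhood-by-time effect or a random slope. The article does not say which visits are responses in the model that yields the T2 test.

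**The concern.** Neighborhoods are the unit of randomization, so the standard error of the effect must contain whatever makes neighborhoods differ in how they move between T1 and T2. A neighborhood intercept that is constant over time does this in some models but not in others.

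The participant effect and the reference to longitudinal observations imply several rows per youth. If T1 is one of those rows and the effect is arm-by-T2, the neighborhood and participant intercepts both drop out of the contrast. Its standard error then rests on the within-youth residual alone. If baseline is a covariate and the rows are post-baseline, the neighborhood intercept stays in the arm contrast, and only visit-to-visit neighborhood variation is left out.

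At stake are the false-positive rate and the interval width of the primary test, and of the secondary outcomes that are also defined as changes.

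**Working it through.** **Inputs from the article.** 16 neighborhoods (12 and 4 by city), 8 per arm; about 45 youth each; 20% attrition, so m = 45 × 0.8 = 36; ICC 0.01; two-sided 5%.

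**Assumptions, not in the article.** Gaussian outcome with total variance 1; within-youth correlation 0.5; no true effect; the share of neighborhood variance that is time-specific, shown from 0 to 100%; ICC 0.05 as a less favourable case.

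**The plan's own figure.** The design effect is 1 + 35 × 0.01 = 1.35. Completers per arm are 360 × 0.8 = 288, so the effective number is 288/1.35 = 213.3. Power for an effect of 0.39 is then 98.1% (z) or 96.0% (t on 14 df), not 80%; the detectable effect at 80% power is 0.27 or 0.29. The stated figure is not reproduced, but the gap is toward more power and does not bear on this point.

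**Notation.** t = time-specific neighborhood variance = share × ICC; c = ICC − t; s = (1 − ICC) × 0.5.

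**Reading A: T1 is a response, test of arm-by-T2.** The true variance of a neighborhood's mean change is 2s/m + 2t. The stated model implies 2(s + t)/m. The ratio is (s + m·t)/(s + t), and the z test rejects with probability 2Φ(−1.96/√ratio). At ICC 0.01, s = 0.495:

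| Share | Ratio | Type I error, formula | Type I error, two simulations |
|---|---|---|---|
| 0% | 1 | 5.0% | 4.6% (one simulation) |
| 20% | (0.495 + 0.072)/0.497 = 1.141 | 6.7% | 6.2%, 6.8% |
| 50% | (0.495 + 0.180)/0.500 = 1.350 | 9.2% | 8.4%, 8.4% |
| 100% | (0.495 + 0.360)/0.505 = 1.693 | 13.2% | 12.7%, 12.4% |

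At ICC 0.05 simulation gave 15.1%, 26.0% and 34.6% for shares of 20%, 50% and 100%.

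**Reading B: baseline is a covariate, T2 and T3 are responses.** With two visits the fitted neighborhood variance settles at c + t/2, because the average over two visits keeps half of t. Leaving aside the variance removed by the baseline covariate, the ratio of implied to true variance at T2 is [c + t/2 + (1 − c − t/2)/36] / [ICC + (1 − ICC)/36]. At ICC 0.01 the denominator is 0.01 + 0.99/36 = 0.0375:

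- 20%: (0.009 + 0.991/36)/0.0375 = 0.974, so 2Φ(−1.96√0.974) = 5.3%
- 50%: (0.0075 + 0.9925/36)/0.0375 = 0.935, so 5.8%
- 100%: (0.005 + 0.995/36)/0.0375 = 0.870, so 6.7%

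One simulation with fitted models and baseline adjustment (1,500 trials per setting) gave, for shares of 0%, 20%, 50% and 100%:

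| ICC | z test | t on 13 df |
|---|---|---|
| 0.01 | 4.7, 6.1, 6.1, 6.8% | 2.7, 3.8, 3.7, 5.4% |
| 0.05 | 5.8, 8.1, 10.1, 13.0% | 4.4, 5.8, 6.8, 9.6% |

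The 13 degrees of freedom are 16 neighborhoods less intercept, city and arm. Allowing for simulation error, at ICC 0.01 the range over shares of 20 to 100% is about 5.5 to 8% (z) and 3 to 6% (t).

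**After the change.** A T2-only model with baseline, city and a neighborhood intercept on 13 df gave 2.9 to 4.0% at ICC 0.01 and 4.5 to 5.5% at ICC 0.05. A neighborhood-level analysis of change on 13 df, which carries between-neighborhood variation in change into the error term, gave 4.2 to 4.3% and 4.6 to 5.8%.

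**The case against.** The strongest objection is that the Abstract is the only place that says how baseline enters, and it says adjustment. That puts baseline on the right-hand side, so the neighborhood intercept is fitted to post-baseline outcomes and does not cancel. Calling an outcome a change and sizing the trial on change does not specify a model, and a baseline-adjusted T2 comparison is a standard analysis of such an outcome. At ICC 0.01 much of the small excess under this reading comes from using z rather than cluster-level degrees of freedom. Visits, covariance structure and degrees of freedom may also be settled in an analysis plan that is not shown.

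Most of this stands. A reader might infer that the stated model discards the design effect, treats youth as individually randomized and therefore always rejects too often. The documents do not support that: it is true only of Reading A, which the Methods wording permits but does not fix.

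Two things remain. The article does state the random structure, so the missing term is not merely a detail left to another document. And the participant effect implies several rows per youth, so the T2-only fit that avoids the problem under baseline adjustment is not quite the model described.

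**Conclusion.** The point holds conditionally. The article names two time-constant random effects and describes the effect both as baseline-adjusted and as a difference in change.

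- If T1 is a response, type I error at ICC 0.01 is about 7%, 8 to 9%, and 12 to 13% for time-specific shares of 20%, 50% and 100%.
- If baseline is a covariate with several post-baseline visits, it is about 5.5 to 8% (z) or 3 to 6% (t on 13 df) at ICC 0.01, and more at ICC 0.05.
- If neighborhoods do not drift differently, nothing is lost on either reading.

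These figures rest on an assumed share, an assumed within-youth correlation of 0.5 and a Gaussian outcome; the article gives none of these. The planned ICC is described as a "conservative within-site correlation of 0.01", and the limitations paragraph accepts that correlations may differ, so the larger values at ICC 0.05 are worth knowing but are not the plan's own case. This is a cheap improvement, not a must-fix error.

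**What to change.** State in one sentence that the primary T2 effect comes from one of two models:

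1. A T2-only model with the baseline score and city as covariates, a neighborhood random intercept and cluster-level degrees of freedom. With one row per youth, the participant effect is dropped.
2. The longitudinal model with an added neighborhood-by-time random effect and cluster-level degrees of freedom, saying whether baseline is a covariate or a response.

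Use the same structure for the secondary outcomes defined as changes.

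The cost is a sentence and at most one model term, with no new data. Confidence intervals become slightly wider. The second option also asks 16 neighborhoods to support one more variance component; if that is estimated at zero the fit falls back to the model now stated, which makes the first option the simpler protection. Primary analysis is expected in January 2027, so the wording can be settled before outcomes are analysed.

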**Conclusions:**

This trial is designed to provide rigorous effectiveness and implementation evidence to inform policy and practice in youth violence prevention. If demonstrated to be effective, FHF could serve as an integrated, scalable model that addresses the social and economic drivers of youth violence and leverages community partnerships for sustainability.

## Introduction

### Background

Youth violence is a pervasive public health problem in the United States, with serious and lasting consequences for physical and mental health [1-4]. Homicide, the most severe consequence of interpersonal violence, remains the third leading cause of death among US adolescents aged 15 to 19 years and the leading cause of death among Black youth in this age group [5,6]. Firearms became the leading cause of death for adolescents aged 14 to 19 years as of 2016, and in 2023, rates for Black adolescents remained far higher than those of other races [7]. Adolescents in high-poverty areas face markedly higher exposure, with homicide rates more than four times higher in high-poverty census tracts than in low-poverty areas [8].

Population-based surveys also document high levels of nonfatal violence and weapon-related risk among high-school students [9]. The National Youth Risk Behavior Surveillance System data show that in 2021, 13% of high school students reported being in a physical fight in the past year, 5% reported carrying a weapon in the past 30 days, and 8% had been threatened or injured with a weapon on school property [10,11]. The 2023 National Youth Risk Behavior Surveillance System provides the most current national estimates, showing that nearly 1 in 8 students experienced at least one form of physical violence in the past year [12].

Youth violence also has lasting developmental and societal consequences, such as impacts on educational attainment [13] and community well-being [14]. Exposure to violence, whether as a victim, perpetrator, or witness, is associated with 2- to 3-fold higher odds of depression and posttraumatic stress disorder [15], increased suicidal ideation [4], and an elevated risk for substance misuse [16]. Longitudinal analyses confirm that cumulative exposure to violence in adolescence predicts an elevated risk for firearm carrying, aggression, and mental health difficulties into early adulthood [17,18]. At the community level, persistent violence has a huge economic cost, erodes perceptions of safety, reduces civic engagement, and perpetuates cycles of social disinvestment [19,20]. Approaches to reduce violence focused on high-school-age youth are urgently needed.

### Prior Work

Evidence from recent population studies [4,5] shows that experiences of multiple forms of violence often co-occur, with cumulative impacts on mental health and behavioral risk. Our work has demonstrated links between victimization and perpetration across various types of violence (eg, peer violence, weapon violence, sexual or relationship violence, bullying, and homophobic teasing) among youth [21].

Youth violence is a complex issue driven by a combination of individual, family, community, and societal factors [22,23]. Individual risk factors include a history of violence, substance abuse, and emotional distress. Family factors, such as mental illness and poverty, can also increase the likelihood of youth violence. Community- and societal-level factors like lack of opportunity, exposure to violence, harmful gender norms, and racial discrimination can contribute to a youth’s involvement in violence. Discrimination contributes both directly to psychological distress and indirectly to violence through mechanisms such as school exclusion and diminished economic opportunity [24-26]. Among young men, restrictive conceptions of masculinity and gender norms, such as the expectation that men “never show weakness,” are associated with significantly higher odds of aggression, bullying, and dating violence [27,28]. Understanding how individual-level risk factors intersect with neighborhood contexts is essential for identifying leverage points for intervention.

At the same time, protective assets can buffer the translation of adversity into violence. Future orientation, a belief in one’s ability to achieve meaningful goals, and supportive relationships with adults and peers have been linked to lower odds of multiple violence outcomes [29,30]. Collective efficacy within neighborhoods can mitigate the impact of exposure to life-threatening violence on youth development [31]. Creating opportunities for youth leadership can function as protective mechanisms, reducing the translation of adversity into violence while building community resilience [32]. Evidence from the United States and abroad indicates that programs explicitly questioning and shifting restrictive views toward men’s and women’s roles and responsibilities—or inequitable social and gender norms—can reduce sexual and relationship violence and HIV risk [33,34]. When paired with employment readiness and opportunity pathways, these programs have the potential to reduce other forms of violence as well [1,34]. These insights point toward multicomponent strategies that simultaneously address multiple drivers and protective assets to reduce violence.

Intervention research is increasingly aligned with this synthesis. National recommendations for preventing youth violence emphasize coordinated strategies that create protective environments, strengthen youth skills, connect youth to caring adults and activities, and support economic opportunities [35]. Results from a randomized controlled trial (RCT) over a decade ago found that engaging youth in high-violence environments in summer programs significantly reduced violence [36]. A recent multisite longitudinal study found that neighborhoods with sustained investment in youth programs saw 18% lower rates of violent offending over a 5-year period, underscoring the potential for upstream prevention [37]. Synergistic models that address cross-cutting risk and protective factors may, therefore, offer a scalable approach to reducing multiple forms of violence simultaneously.

In our prior work, a community-based program promoting a positive and caring sense of manhood for adolescent boys and young men—called “Manhood 2.0”—and a related job readiness comparison, both reduced sexual violence perpetration [34]. This suggests promise for cross-cutting reductions in youth violence when gender, racial, and economic drivers are addressed together [38,39]. Other job-readiness and mentoring programs have also shown promise for improving prosocial engagement among youth in environments of high violence exposure, though effects on violence outcomes have been heterogeneous, again suggesting the value of an integrated model that addresses multiple drivers simultaneously [35].

At this point, significant gaps remain in addressing youth violence. Few rigorously evaluated US programs intentionally integrate content that simultaneously addresses multiple drivers of youth violence. Moreover, relatively little research interrogates mechanisms of change (eg, whether shifts in attitudes, gains in future orientation, and increased job skills explain reductions in violence involvement) or examines moderators such as prior exposure to violence or structural disadvantage. A pragmatic, community-delivered intervention evaluated through a cluster-randomized design can address these gaps while producing evidence relevant for scale and sustainability. In short, youth violence remains a pressing public health priority, and rigorous evaluation of promising, theory-driven, and pragmatic approaches is necessary to determine whether such an integrated model reduces violence and to identify pathways of effect.

### Study Objectives

This protocol describes the rationale and design for a 3-year, 2-arm, community-partnered cluster–randomized trial of *Forging Hopeful Futures* (FHF), an intervention that integrates curriculum content on violence prevention and conflict resolution, critical-consciousness building around key social drivers, youth leadership, and job-readiness with facilitated connections to employment and mentoring. The trial enrolls high school adolescents (aged 14‐19 y) in neighborhoods with limited resources and high violence exposure in Pittsburgh, Pennsylvania, and the Washington, DC, region. Guided by social determinants of health theories and implementation science frameworks, the study has 4 objectives. First, to assess whether youth in neighborhoods assigned to FHF, relative to enhanced usual programming, exhibit greater reductions in violence involvement (experience and perpetration). Second, to examine whether changes in key secondary outcomes—such as mental health, gender attitudes, and improvements in future orientation—mediate and help explain intervention effects on violence outcomes. Third, to evaluate moderation of intervention effects by baseline profiles, including prior violence exposure and neighborhood disadvantage, thereby identifying for whom FHF is most effective. Fourth, to document implementation processes, feasibility, and fidelity, informing future scale-up and adaptation.

Taken together, the study is designed to advance evidence for preventing youth violence and promoting healthy development among adolescents living in communities with limited resources. By addressing the intertwined influences of relationship dynamics, community violence, and economic challenges, this study aims to advance the science of youth violence prevention and inform policies and programs that promote safety and thriving for marginalized adolescents.

